**Table 4-3 Simon 2-stage design futility criteria for**

| The alternative vs null objective response rate rates (P1 vs P0) | Futility stage 1 | Futility stage 2 | Applies to |
|------------------------------------------------------------------|------------------|------------------|------------|
|                                                                  |                  |                  |            |
|                                                                  |                  |                  |            |
|                                                                  |                  |                  |            |

Arms B are for single agent D-1553 treatment and Arms F are for combination treatments, as follows:

- 
- Arm B: solid tumors other than NSCLC treated with D-1553 single agent at RP2D;
- 
- 
- 
- 
- Arm F: CRC, D-1553 in combination with cetuximab

Upon completion of Phase 1a (single agent dose escalation), Phase 2 Arms B may be started, while Phase 2 Arms F may be started once Phase 1b (dose combination) is completed. The sequence of enrollment to each group or arm will be communicated to investigational sites by study team. Each arm will enroll approximately 30 subjects for evaluation of safety and efficacy in subjects with KRASG12C bearing solid tumors. If 1 or more arms demonstrate significant antitumor activity that

Each subject will receive an oral dose of D-1553 at RP2D. Each 21- or 28-day period will be considered as 1 treatment cycle. Subjects may continue with daily administration of D-1553 until disease progression, unacceptable treatment-related toxicity, withdrawal of consent or discontinuation from the study for other reasons, whichever occurs first. In the combination arms, D-1553 may be continued at the same dose level after the combination regimen is completed, if the investigator considers it is in the best interest of the subject, after consulting with the sponsor's medical representative. [REDACTED]

Subjects who do not have disease progression on study will be followed for tumor assessment, approximately every 12 weeks ( $\pm 2$  weeks), until disease progression, death, lost to follow-up, start of another anticancer therapy, or other reasons that a follow-up is not possible. Subjects will be followed for survival status monthly ( $\pm 2$  weeks), until death, lost to follow-up or other reasons that a follow-up is not possible. The follow-up can be done via telephone call.

### Targeted Therapy in Arm F

In combination with D-1553 (once daily or twice daily), subjects will receive an intravenous dose of cetuximab (400 mg/m^2 initial dose, 120-minute IV infusion on Cycle 1 Day 1), then 250 mg/m^2 (60-minute IV infusion) once weekly. Thereafter, each 21-day cycle will be considered as 1 treatment cycle. D-1553 and cetuximab may continue until disease progression, unacceptable treatment related toxicity, withdrawal of consent or discontinuation from study for other reasons, whichever occurs first.

#### 4.1.4 Dose Escalation and Stopping Rules

This study will evaluate the safety, tolerability, PK and efficacy of D-1553 administered as a single agent and in combination with [REDACTED] targeted therapy in subjects with advanced or metastatic solid tumors with KRASG12C mutation. In the Phase 1 part of the study, the design requires careful multiple dose level evaluations and dose escalation based on pre-set safety evaluation criteria. After the MTD or highest planned dose of D-1553 as a single agent or in combination regimen is reached, the study will go into Phase 2 evaluation to further assess the

The safety assessments for the study are accepted measures for ensuring the safety of subjects during a clinical study. The PK sampling schedule is considered appropriate given the information available from preclinical studies. The rationale for the clinical study is presented in [Section 2.7](#).

The MTD is the highest dose level of D-1553 that doesn't cause unacceptable side effects. During dose escalation in Phase 1, if 2 out of 6 subjects experience DLTs (side effects that prevent a dose increase) at a given dose level during the first cycle of the therapy, then the MTD has been exceeded and dose escalation will be stopped. The MTD will be determined as the next lower dose level. The RP2D will be at or below MTD.

[REDACTED]

[REDACTED]

[REDACTED]

[REDACTED]

- [REDACTED]
- [REDACTED]
- [REDACTED]  
[REDACTED]
- [REDACTED] [REDACTED]  
[REDACTED]
- [REDACTED]
- [REDACTED]

[REDACTED]

[REDACTED]

■ [REDACTED]  
[REDACTED]  
[REDACTED]

■ [REDACTED]  
[REDACTED]

■ [REDACTED]  
[REDACTED]  
[REDACTED] ■ [REDACTED] [REDACTED] [REDACTED] [REDACTED] [REDACTED] [REDACTED] [REDACTED]  
[REDACTED]

[REDACTED]

■ [REDACTED]  
■ [REDACTED]  
[REDACTED]

■ [REDACTED]  
■ [REDACTED]  
■ [REDACTED]  
■ [REDACTED] [REDACTED] [REDACTED] [REDACTED] [REDACTED] [REDACTED] [REDACTED]  
[REDACTED]

■ [REDACTED]  
[REDACTED]

■ [REDACTED] [REDACTED]  
[REDACTED]  
[REDACTED] [REDACTED]  
[REDACTED]  
[REDACTED]

■ [REDACTED]

■ [REDACTED]  
[REDACTED]

■ [REDACTED]

■ [REDACTED] [REDACTED] [REDACTED] [REDACTED] [REDACTED] [REDACTED] [REDACTED]  
[REDACTED]  
[REDACTED]

■ [REDACTED]  
[REDACTED]

■ [REDACTED]

■ [REDACTED]

■ [REDACTED]  
[REDACTED]

#### **4.2.2 Dose-limiting toxicity evaluation**

The DLT evaluation period is the first cycle of treatment and starts from treatment cycle 1/Day 1. If a subject is not evaluable for DLT due to reasons other than treatment-related toxicities in treatment cycle 1, then an additional subject will be enrolled in the cohort for replacement.

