**Table 4-1 Dose Escalation Cohorts For Phase 1a**

| Cohorts (once daily)  | Cohort 1   | Cohort 2   | Cohort 3   | Cohort 4    |                    |                    |
|------------------------------|-------------------|-------------------|-------------------|--------------------|--------------------|--------------------|
| Dose                  | 150 mg once daily | 300 mg once daily | 600 mg once daily | 1200 mg once daily |                    |                    |
| Cohorts (twice daily) |                   |                   |                   | Cohort 5    | Cohort 6    | Cohort 7    |
| Dose                  |                   |                   |                   | 400 mg twice daily | 600 mg twice daily | 800 mg twice daily |

The starting dose of 150 mg once daily in human was selected based on the information derived from nonclinical safety pharmacology and toxicology studies. This dose has been intentionally chosen as a conservative starting point to maximize safety margins according to the standard DeGeorge method, [REDACTED]

Accelerated titration (single subject per cohort) will be used for Cohorts 1 and 2 until one Grade 2 or higher at least possibly TRAE occurs during the DLT observation period (treatment cycle 1), after which another 2 subjects will be enrolled in the same cohort and the dose escalation will be converted to follow conventional 3+3 design. If no Grade 2 or higher TRAE occurs in Cohorts 1

and 2, Cohort 3 will start to follow the conventional 3+3 design. Cohorts 5 to 7 will always follow the conventional 3+3 dose escalation design.

The conventional 3+3 dose escalation will be conducted as follows:

Three subjects will be enrolled and treated in the current cohort and observed for DLT during the DLT observation period (treatment cycle 1).

- If there is no DLT, the next higher dose cohort can start.
- If there is one DLT, another 3 subjects will be enrolled and treated.
  - If there is no more than one DLT in 6 subjects, the next higher dose cohort can start.
  - If there are more than one DLTs in 6 subjects, the MTD has been exceeded and the next lower dose will be the MTD or an intermediate dose may be evaluated.
- If there are two or more DLTs, the MTD has been exceeded and the next lower dose will be the MTD or an intermediate dose may be evaluated.

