This 3+3 dose escalation scheme will be repeated until the MTD is determined or the highest planned dose is reached.

Each subject will receive daily oral doses of D-1553 (once daily for Cohorts 1 to 4 and twice daily for Cohorts 5 to 7) from Day 1 to Day 21 on an empty stomach [REDACTED]

[REDACTED] Each 21-day period will be considered as 1 treatment cycle. Subjects may continue daily D-1553 until disease progression, unacceptable treatment related toxicity, withdrawal of consent or discontinuation for any reason, whichever occurs first. Safety will be assessed throughout treatment cycles and during followup periods. Dose limiting toxicity will be evaluated during the 1st treatment cycle. Pharmacokinetic parameters ( $AUC_{0-t}$ ,  $AUC_{inf}$ , MRT,  $C_{max}$ ,  $t_{max}$ ,  $C_{min}$ ,  $t_{1/2}$ ,  $V_{dss}/F$  and  $CL/F$ ) will be evaluated during the 1st and 3rd treatment cycles. PK timepoints of subsequent cohorts may be adjusted based on PK results from Cohort 1 and/or Cohort 2. Tumor assessments will be performed at screening and every 2 treatment cycles for the first 8 treatment cycles and every 3 treatment cycles thereafter until disease progression.

An SRC, [REDACTED] will regularly assess the safety of D-1553 and its combination therapy throughout the study. After completion of the 1st treatment cycle in each cohort of the conventional 3+3 dose escalation scheme, the SRC will review all available data to recommend whether or not to proceed to the next cohort. The SRC may recommend to lower the increment for the next dose level or add additional cohorts at the dose escalation meeting, based on the safety and PK results. Intermediate dose escalation levels (between Cohorts 1 and 4; Cohorts 5 and 7) may be evaluated during the study, as shown in Table 4-2.

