Each subject will receive an oral dose of D-1553 (once-daily or twice-daily) at the assigned dose, combined with cetuximab in a 21-day cycle. Subjects may continue study treatment until disease progression, unacceptable treatment -related toxicity, withdrawal of consent or discontinuation from study for other reasons, whichever occurs first.

Safety will be assessed throughout treatment cycles and follow-up periods. Pharmacokinetic parameters (AUC,  $-C_{max}$ ,  $t_{max}$ ,  $C_{min}$ ,  $t_{1/2}$ ,  $V_{dss}/F$  and  $CL/F$ ) will be evaluated during the 1st and 3rd treatment cycles. Tumor assessments will be performed at screening every 2 treatment cycles for the first 8 treatment cycles and every 3 treatment cycles thereafter until disease progression.

Once a PR or CR is observed, a confirmatory tumor assessment is recommended to be performed with at least 4 weeks' interval per RECIST 1.1.

[illegible]

#### 4.1.3 Phase 2

The Phase 2 portion is a 6-arm, parallel, open-label study to evaluate the efficacy of D-1553 single agent and combination treatments in subjects with advanced or metastatic solid tumors with KRASG12C.

The futility criteria are based on assumptions for the ORR for the SOC and the expected effect based on the addition of D-1553 to the SOC.

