### 6.2.7 Dose Interruptions/Delay/Reductions

Dose reductions of D-1553 may be required based on the worst toxicity experienced. In the event that a study drug related Grade 3 or higher toxicity occurs, defined in the NCI CTCAE v5.0, administration of D-1553 should be held until the drug related toxicity has resolved to grade 1 or baseline. Upon resolution of the toxicity or return to baseline, the subject should resume their current assigned dose of D-1553 or at the next lower dose level after discussion with sponsor. The following guidance can be used:

- After Cycle 1 Day 1, a treatment delay or dose interruption of more than one treatment cycle (21 or 28 days after the current cycle) will result in treatment discontinuation unless the subject is receiving clinical benefit as judged by the investigator and after discussion with the sponsor.
- Doses delayed or missed will not be made up (i.e., cycles will not be prolonged beyond the 21st or 28th calendar day in order to make up any missed doses).
- If a treatment interruption continues beyond Day 21 or Day 28 of the current cycle, then the day when treatment is resumed will be counted as Day 1 of the next cycle.

For subjects who experience a recurrent study drug related Grade 3 or higher toxicity, a discussion between the sponsor and investigator will occur to determine whether the subject should continue in the study. For any subject experiencing a Grade 3-4 toxicity, treatment should be resumed at next lower dose level after toxicity resolves to Grade 1 or baseline. A subject who experiences the same serious adverse event (SAE) of the same NCI CTCAE toxicity grade or higher related to D-1553 must discontinue the treatment immediately. Any subject with liver function test abnormalities meeting Hy's Law\* criteria [REDACTED]

[REDACTED] must be permanently discontinued,  
[REDACTED]  
[REDACTED]  
[REDACTED]

\* Hy's Law: ALT or AST  $\geq 3 \times$  ULN, TBIL  $\geq 2 \times$  ULN in the absence of cholestasis (serum alkaline phosphatase [ALP]  $> 2 \times$  ULN), and there are no other reasons to explain the combined elevation of aminotransferase and TBIL.

[REDACTED]

In combination cohorts, the combination drugs (other than D-1553) may have dose interruption, delay, reduction or other modifications according to their prescribing information.

[REDACTED]

[REDACTED]

\_\_\_\_\_

\_\_\_\_\_

[REDACTED]

\_\_\_\_\_

\_\_\_\_\_

[illegible]

[illegible]

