## **7 STUDY PROCEDURES**

Study procedures and their time points are summarized in the Schedule of Assessments (see Table 1-1 through Table 1-3). Refer to the investigational product, laboratory and site imaging manuals for detailed collection and handling procedures.

Adherence to the study design requirements, including those specified in the Schedule of Assessments, is essential and required for study conduct.

A signed and dated IRB/IEC approved ICF must be obtained prior to performing any study specific procedures, including discontinuing standard therapy for observing study specific washout periods.

Subjects will be seen in the clinic for study evaluations. During all visits' invasive procedures like blood draws or biopsies should be completed after ECGs and vital signs.

Blood samples for biomarker and PK assessments should be drawn from a peripheral vein and not from a central venous catheter. The study specific lab manual will provide additional detail on lab sampling and handling requirements.

Furthermore, start of a treatment can be delayed for administrative/logistical reasons for up to 7 days to allow for appropriate scheduling after discussion with and final approval by sponsor.

Any missed visits, tests not done, or examinations that are not conducted must be reported as such on the eCRFs. Subsequent study visits should resume on the original schedule. Missed assessments at prior visits should not be duplicated at subsequent visits. Every effort should be taken to collect all biomarker and PK samples as described in the schedule of assessments.

Additional procedures deemed necessary as part of standard of care or as required by local laws and regulations may be performed at the Investigator's discretion.

At selected sites, up to a total of 30 phase 2 subjects will also be consented to have intensive PK and ECG data collected according to Table 1-6.

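### In Phase 1 the Cycle 2 Day 1 visit may be held from Day 18, so up to 4 of the 21 DLT days can lack a scheduled assessment before the escalation decision

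*Protocol*

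**What the plan says.** Protocol 4.2.2 sets the DLT period by reference to the cycle: "The DLT evaluation period is the first cycle of treatment and starts from treatment cycle 1/Day 1". The 3+3 rules in 4.1.1 use the same period.

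The cycle length is given elsewhere. For Phase 1a, 4.1.1 has dosing "from Day 1 to Day 21 on an empty stomach" and adds: "Each 21-day period will be considered as 1 treatment cycle". For Phase 1b, the visible text of 4.1.2 refers to "cetuximab in a 21-day cycle", while the header of Table 1-2 allows 21 or 28 days and its footnote 16 makes the length depend on the combination.

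In Tables 1-1 and 1-2 the visit-window row gives ±4 days both for Cycle 1 Day 14 and for Day 1 of Cycle 2 and later. Laboratory tests and the physical examination are scheduled at both visits. Table 1-2 adds laboratory tests on Day 8 (±2). From Cycle 2 onward, Day 1 is the only scheduled visit in each cycle. D-1553 is dispensed on Day 1 of each cycle.

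Under 4.1.1 and 4.1.2 the SRC reviews a cohort after the first cycle is completed.

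**The concern.** The visit that closes out DLT observation can be held before the DLT period is over. At the nominal Day 22, its tests and examination look back over the whole 21 days. On Day 18 they cannot cover what follows, and nothing further is scheduled until Cycle 3. A laboratory-defined toxicity arising on Days 18 to 21 could then go undetected when the SRC reviews the cohort.

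Because drug is dispensed at this visit and the column is labelled Day 1 of the cycle, a site might also take an early visit as the start of Cycle 2. Nothing in the visible text of 4.2.2 tells it otherwise.

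DLT incidence is a Phase 1 primary endpoint (3.2.1). It drives the 3+3 decisions, the MTD and the dose taken into Phase 2. Cohorts are of 3 to 6 subjects, so one missed event can change a decision.

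**Working it through.** **Inputs**
- Cycle length: 21 days in Phase 1a (4.1.1); 21 or 28 days in Phase 1b (Table 1-2 header).
- Visit window: ±4 days for Cycle 1 Day 14 and for Day 1 of Cycle 2 and later (Tables 1-1 and 1-2).
- The protocol has no computed figure to reproduce here; the 21-day cycle is a definition.

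**21-day cycle**
- Cycle 2 Day 1, nominal: 21 + 1 = Day 22. Range: 22 − 4 = Day 18 to 22 + 4 = Day 26.
- Full days before the earliest visit: 18 − 1 = 17.
- DLT days not fully covered: 21 − 17 = 4 (Days 18 to 21); 4/21 = 19%.
- Cycle 1 Day 14 visit: latest 14 + 4 = Day 18. The two visits can therefore fall on the same day.
- Cycle 3 Day 1, nominal: 42 + 1 = Day 43. Range: Day 39 to Day 47.
- Interval from a Day 18 visit to the next scheduled laboratory tests: 39 − 18 = 21 days to 47 − 18 = 29 days.

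**28-day cycle (Phase 1b regimens, where used)**
- Cycle 2 Day 1, nominal: Day 29; earliest 29 − 4 = Day 25.
- Full days before the earliest visit: 24. Days not fully covered: 28 − 24 = 4; 4/28 = 14%.

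**Does an early visit end Cycle 1?** The text points against it.
- 4.1.1 fixes the cycle at 21 days.
- The ±4 sits in the visit-window row, so it is a tolerance on attendance.
- Section 7 says of missed visits: "Subsequent study visits should resume on the original schedule". That treats the calendar as fixed.
- The only visible rule that moves a cycle start is in 6.2.7. It applies when a dose hold outlasts the 21 or 28 days, and it ties the new cycle to the restart of dosing: "the day when treatment is resumed will be counted as Day 1 of the next cycle". It moves the start later.

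On this reading Days 18 to 21 belong to Cycle 1 even when the visit is on Day 18, and a DLT on those days counts. What shrinks is scheduled ascertainment.

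**The case against.** The strongest reply is that the DLT period is already fixed: 21 days in Phase 1a, with the ±4 only a visit tolerance. That stands. It defeats the reading, which a reader might infer, that the window closes after 17 days and that toxicities on Days 18 to 21 drop out of the 3+3 count. No visible sentence says so. The DLT criteria in 4.2.1 are redacted and may contain a day count, so the length cannot be called undefined either.

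A reader might also infer from 6.2.7 that a dose hold keeps Cycle 1, and hence the DLT period, open for about 42 days (21 + 21). That section says only when the next cycle starts. It does not assign the gap days to Cycle 1, and it says cycles are not prolonged to make up missed doses.

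Nor can escalation probabilities be offered as an expected effect. With true DLT risk p over 21 days and a constant hazard, the 17-day risk is 1 − (1 − p)^(17/21), and the chance of passing a dose level is (1 − p)^3 + 3p(1 − p)^5. This rises from 0.709 to 0.783 at p = 0.20 and from 0.434 to 0.542 at p = 0.33. Both p and the hazard are assumptions. The figures also require every subject to attend 4 days early and no DLT on Days 18 to 21 to be counted. They are assumed worst cases.

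There are safeguards. AEs are collected continuously until 30 days after the last dose, unless other anti-tumor therapy starts sooner (8.1.1). Weekly or more frequent laboratory tests are allowed at the investigator's discretion (Tables 1-1 and 1-2, footnote 11). The SRC reviews all available data (4.1.1). Cetuximab subjects attend weekly for infusions (6.5). These reduce the gap but do not close it: an asymptomatic laboratory abnormality needs a test, and none is scheduled on those days.

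**Conclusion.** The point holds as a small weakness in ascertainment of a primary safety endpoint. The schedule allows a subject to be counted DLT-free for the SRC decision with no scheduled laboratory test or examination after Day 18 of a 21-day period. Up to 4 of 21 days are affected (4 of 28 in a 28-day regimen), and only in subjects seen early. How many would be seen early is unknown.

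The missing statement in 4.2.2 about early visits is a matter of clarity, subject to whatever the redacted 4.2.1 contains. The documents do not show that DLTs are excluded from the count, that the window lengthens with a hold, or that escalation is biased by any particular amount. No sample size, error rate or power depends on this.

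Section 2.10 cites monotherapy results at 600 mg twice daily as of 8 June 2022, so the practical gain may lie mainly in any Phase 1b cohorts still to be enrolled.

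**What to change.** 1. In Tables 1-1 and 1-2, set the Cycle 2 Day 1 visit window to 0/+4 days for DLT-evaluable Phase 1 subjects. The visit then falls on Days 22 to 26 (Days 29 to 33 in a 28-day cycle), inside the range already allowed. Later cycles keep ±4.
2. In 4.2.2, state that the DLT period is the full nominal calendar length of Cycle 1 from first dose (21 days, or 28 for 28-day regimens), unchanged by visit windows. Give the length for each Phase 1b group. This is clarification only.

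The cost is one table footnote, one sentence and slightly less scheduling flexibility at one visit. The latest permitted date does not change, so the latest point at which a cohort becomes ready for SRC review is not pushed back.

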#### **4.3 Study Termination Criteria**

The estimated duration of the study is contingent on the number of dose levels evaluated in the dose escalation. The study will be discontinued in the event of any new findings that indicate a relevant deterioration of the risk-benefit relationship that would render continuation of the study unjustifiable, or for administrative reasons by the sponsor.

## 5 STUDY POPULATION

Prospective approval of protocol deviations to recruitment and enrollment criteria, also known as protocol waivers or exemptions, is not permitted.

The study population will consist of subjects with advanced or metastatic solid tumors with KRASG12C mutation. Subjects must be able to provide written consent and meet all the inclusion criteria and none of the exclusion criteria.

### 5.1 Inclusion Criteria

Subjects are eligible to be included in the study only if all of the following criteria apply:

1. Subject must be fully informed about their illness and the investigational nature of the study protocol (including foreseeable risks and possible side effects) and must have signed and dated an Institutional Review Board (IRB) /Independent Ethics Committee (IEC) approved Informed Consent Form (ICF) that is in accordance with regulatory and ethics guidelines and it must be obtained before the performance of any protocol related procedures or tests.
2. Subject is male or female of at least 18 years of age at the time of signing informed consent.
3. Subject must be willing and able to comply with all scheduled visits, treatment, laboratory tests, be able to take oral medication and accept other requirements of the study.
4. Subject with histologically or cytologically proven, locally advanced, unresectable and/or metastatic solid tumor.
5. Subject has KRASG12C mutation in tumor tissue, blood, pleural effusion or other samples containing cancer cells or DNA. [REDACTED]  
[REDACTED]
6. Phase 2 subjects must be able to provide a sufficient amount of representative tumor specimen (archival sample collected within 5 years) and ctDNA samples for central laboratory testing of KRAS mutation status. Subject with KRASG12C mutation in tumor or ctDNA samples local testing is acceptable for eligibility; all patients in Phase 2 study will have confirmation of KRASG12C mutation by Sponsor-designated central laboratory [REDACTED]  
[REDACTED]
7. Subject has tumor type requirement as follows:
  - a. Phase 1a: advanced or metastatic solid tumors for which no standard treatment is available or the subject is refractory to or intolerant of existing standard treatment;

[REDACTED]  
[REDACTED] [REDACTED] [REDACTED] [REDACTED] [REDACTED] [REDACTED] [REDACTED] [REDACTED] [REDACTED]  
[REDACTED]

- [REDACTED]
- [REDACTED]
- [REDACTED]
- [REDACTED]
- [REDACTED]
- [REDACTED]
- [REDACTED]
- [REDACTED]
- [REDACTED]
- [REDACTED]
- f. Phase 2 Arm B: advanced or metastatic solid tumors other than NSCLC for which no standard treatment is available or the subject is refractory to or intolerant of existing standard treatment;
- g. [REDACTED] Phase 2 Arm F: advanced or metastatic CRC that have progression of disease after at least 1 prior regimens:
- Disease relapse during treatment or within 6 months following adjuvant therapy will be considered advanced or metastatic disease;
  - Patients who have received 2 prior regimens (i.e. those entering the study in the 3rd line setting), must have received oxaliplatin unless it was contraindicated due to underlying conditions.
8. Subject has measurable disease according to RECIST, v1.1. For Phase 1 portion, subject with evaluable disease according to RECIST, v1.1 is also acceptable.
9. Subject in Phase 1 has an Eastern Cooperative Oncology Group (ECOG) performance status of Grade  $\leq 2$ , [REDACTED]. Subject in Phase 2 has an ECOG performance status of Grade 0 or 1.
10. Subject has adequate hematologic function, defined as:
- Platelet count  $\geq 100 \times 10^9/L$ ;
  - Hemoglobin level  $\geq 8.0$  g/dL. [REDACTED]
- [REDACTED]
- [REDACTED] Participants can be on stable dose of erythropoietin ( $\geq$  approximately 3 months);

- Absolute neutrophil count  $\geq 1.5 \times 10^9/\text{L}$ .

[REDACTED]

11. Subject has adequate renal function, defined as creatinine clearance  $\geq 60 \text{ mL/min}$ , as calculated using the modified Cockcroft Gault equation or other institutional standard formula, or creatinine  $\leq 1.5 \times$  upper limit of normal (ULN).

12. Subject has adequate liver function, defined as:

- Aspartate aminotransferase (AST) levels  $\leq 2.5 \times \text{ULN}$  (if liver metastases are present,  $\leq 5 \times \text{ULN}$ );
- Alanine aminotransferase (ALT) levels  $\leq 2.5 \times \text{ULN}$  (if liver metastases are present,  $\leq 5 \times \text{ULN}$ );
- Total bilirubin  $\leq 1.5 \times \text{ULN}$  (not applicable to subjects with Gilbert's syndrome).

- [REDACTED]

■ [REDACTED]

■ [REDACTED]

13. Subject has adequate coagulation function, defined as prothrombin time and activated partial thromboplastin time  $\leq 1.5 \times \text{ULN}$ , and International normalized ratio (INR)  $\leq 1.5$ . For subjects on anticoagulation therapy, the INR should be  $< 3.0$  or within the target range of anticoagulation therapy if applicable (INR should be used instead of prothrombin time for subjects on anticoagulation therapy).

14. [REDACTED]

15. Female of childbearing potential must agree to abstain or use effective contraception methods from the time of signing ICF and for the duration of study participation through 6 months after the last dose of study drug. Acceptable contraceptive methods include: oral, injected or implanted hormonal methods of contraception; intrauterine device or intrauterine system; occlusive cap (diaphragm or cervical/vault caps) with spermicide together with male condom. If needed, investigators can select from the above contraception methods to meet the country or institutional standards of an effective contraception method.

- A female subject of childbearing potential is any woman, regardless of sexual orientation, who meets the following criteria: a) not surgically sterile with procedures like tubal ligation, hysterectomy, bilateral salpingectomy or bilateral oophorectomy; or b) not been naturally postmenopausal for at least 12 consecutive months (i.e., has had menses at any time in the preceding 12 consecutive months).
16. Male subjects must agree to abstain, be surgically sterilized, or agree to use an effective contraceptive method from the time of signing of ICF and for the duration of study participation through 6 months after the last dose of study drug. Effective contraceptive methods include: a) simultaneous use of condom, and for the female partner, hormonal contraceptives or intrauterine contraceptive device (used since at least 4 weeks prior to dosing); b) simultaneous use of condom, and for the female partner, diaphragm or cervical/vault caps with spermicide. If needed, investigators can select from the above contraception methods to meet the country or institutional standards of an effective contraception method.

